## Methods/design

### Study design

The study is a parallel multi-center randomized controlled trial. It will compare the combination of acupuncture and Western medicine treatments with standard Western stroke treatment given alone during the acute phase (24 weeks) after stroke. The Barthel Index (BI) and Stroke-Specific Quality Of Life (SS-QOL) will be assessed as primary outcome measures, and the secondary outcome measures are the National Institutes of Health Stroke Scale (NIHSS) and modified Rankin Scale (mRS). All assessments will be conducted at baseline and at weeks 4, 12 and 24 of follow-up. The study design is detailed in Figure 1.

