### Interventions

A total of 328 patients in the acute stage of cerebral apoplexy will be recruited. The patients are randomly divided into two different groups: 1) the intervention group and 2) the control group. The intervention group will receive acupuncture treatment in addition to the Western medicine standard treatment for 2 weeks and the secondary prevention treatment for 22 weeks, and the control group will receive standard Western-medicine therapy for 2 weeks and the secondary prevention treatment for 22 weeks. Both groups will be evaluated at baseline and at 4, 12 and 24 weeks of treatment.

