### Statistical analysis

The statistical analysis will be performed by the Epidemiological Research Center of the Third Affiliated Hospital of Beijing University.

The quantitative data are presented as mean ± standard deviation and will be analyzed using analysis of variance when normally distributed. Non-parametric data will be analyzed using the Wilcoxon test with repeated measures. Enumeration data are presented as frequencies or ratios. If the outcome variables are two-way 2×2 contingency tables, chi-square tests or Fisher exact probability tests will be performed. If they are one-way 2×4 ordered data, Ridit analyses will be performed.

Statistical analyses will be conducted using SPSS version 13.0 (SPSS, Chicago, IL, USA). The P-value cut-off for statistical significance is defined as *P* < 0.05, and all statistical tests are two-tailed.

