Recovery of function after stroke is a long steady process that continues for several weeks or even months before reaching a stable phase. The effects of acupuncture occur within the same time frame. Several previous studies did not show any beneficial effect of acupuncture, and this may in part be explained by an assessment of efficacy too soon after acupuncture treatment (in most cases 2–3 weeks after stroke) [22,23]. An assessment or reassessment at a minimum of 4 weeks, and ideally at least 3 to 6 months after the completion of treatment is essential. We followed the time course of the normal process of stroke recovery in designing our study protocol. Thus, we will assess efficacy at baseline and at 4, 12 and 24 weeks after acupuncture intervention.

The primary endpoint for this study is the change in the quality of life in the intervention and control groups, from baseline to 4, 12 and 24 weeks post-therapy. Neurological deficits, disability, and dependence in activities of daily living will be evaluated by NIHSS and mRS as the secondary endpoints.

Many acupuncturists consider the main effect of acupuncture on the human body after stroke to be the rehabilitation of motor function, whereas few have considered the patients’ life quality, which includes factors such as dependence in activities of daily living, feeding, dressing, and continence of bowels and bladder. To address this, we will use the BI and SS-QOL questionnaires to measure the quality of life as the primary outcomes.

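### The Wilcoxon procedure named for non-normal scores is, read literally, a within-patient test that does not compare the arms; on no reading does it fix a between-arm analysis

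*Protocol article*

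**What the plan says.** The Statistical analysis section of the protocol article splits quantitative outcomes by distribution. Normally distributed data "will be analyzed using analysis of variance when normally distributed"; the factors of that analysis are not given. For the rest, "Non-parametric data will be analyzed using the Wilcoxon test with repeated measures". The section does not say whether signed-rank or rank-sum is meant, and it does not name arm as the factor compared. It sets the threshold for all tests: "The P-value cut-off for statistical significance is defined as *P* < 0.05, and all statistical tests are two-tailed".

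The purpose of the trial is clear from the Study design section: "It will compare the combination of acupuncture and Western medicine treatments with standard Western stroke treatment given alone". Assessments are at baseline and weeks 4, 12 and 24. The Discussion words the primary endpoint as change from baseline in each of the two groups, without spelling out a contrast between them. It also says: "Recovery of function after stroke is a long steady process that continues for several weeks or even months before reaching a stable phase".

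**The concern.** The trial asks whether patients given acupuncture do better than patients not given it. A paired Wilcoxon test asks whether patients in one group changed between two visits. After acute stroke both groups are expected to improve, as the Discussion itself says, so a small P value within an arm mostly reflects recovery.

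The rule may well be used. The Barthel Index has a maximum of 100 and the NIHSS a minimum of 0. As patients recover, scores can pile up at those limits and fail a normality check. The Barthel Index is a primary outcome. Under the paired reading, the hypothesis tested for such a score would depend on the shape of its data.

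**Working it through.** The article gives no effect size, SD or power for its sample size, so there is no stated figure to reproduce. The check is about which hypothesis each candidate test addresses, and how it behaves when acupuncture does nothing.

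**The two readings side by side**

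- *Signed-rank (paired).* Input: one group, two visits. Null hypothesis: no change over time in that group. Arm does not enter.
- *Rank-sum (two-sample).* Input: two groups, one value per patient. Null hypothesis: no difference between arms. Repeated visits do not enter, so someone must still choose raw score or change, and the visit.

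The design has two arms and four visits. Neither test takes both.

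**Inputs from the article**

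- Total sample: "A total of 328 patients in the acute stage of cerebral apoplexy will be recruited" (Interventions).
- Two groups (Interventions), ratio not stated. Assuming 1:1, 328 / 2 = 164 per arm.
- Two-sided 0.05 (Statistical analysis).

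**Assumptions, not in the article**

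- Barthel-like score from 0 to 100 in steps of 5, baseline mean 50, SD 25, correlation 0.6 between baseline and follow-up.
- Recovery m, in SD of the score, equal in both arms (no acupuncture effect). The article gives no size for recovery, so a range is shown.

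**Approximate formula for the paired test**

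The SD of the change, in units of the score SD, is √(2(1 − 0.6)) = √0.8 = 0.894. The standardised change is δ = m / 0.894. For roughly normal changes,

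P(significant within an arm) ≈ Φ(δ × √n × √(3/π) − 1.96), with √164 = 12.81 and √(3/π) = 0.977.

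- m = 0.1 (2.5 points): δ = 0.112; 0.112 × 12.81 × 0.977 = 1.40; Φ(−0.56) = 0.29
- m = 0.2 (5 points): δ = 0.224; 2.80; Φ(0.84) = 0.80
- m = 0.3 (7.5 points): δ = 0.335; 4.20; Φ(2.24) = 0.99
- m = 0.5 (12.5 points): δ = 0.559; 7.00; Φ(5.04) ≈ 1.00

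**Simulation with the rounded, bounded score (2000 runs per row, no acupuncture effect)**

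| Recovery m | Signed-rank, acupuncture arm | Signed-rank, control arm | Significant in acupuncture arm only | Rank-sum on change, between arms |
|---|---|---|---|---|
| 0 | 5.4% | 4.6% | 5.0% | 5.2% |
| 0.1 | 30.6% | 28.6% | 21.2% | 4.2% |
| 0.2 | 79.0% | 79.0% | 17.0% | 5.6% |
| 0.3 | 98.2% | 98.2% | 1.8% | 4.6% |
| 0.5 | 100% | 100% | 0% | 5.2% |

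Formula and simulation agree. If recovery of 0.3 is instead measured in SD of the change score, the formula gives 0.3 × 12.81 × 0.977 = 3.75 and Φ(1.79) = 0.96, and a smaller simulation (500 runs) gave about 94%. Hence about 94-100% for 0.3-0.5 SD across the two scalings.

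**Setting the two within-arm P values against each other does not help.** With no effect, the chance of significance in the acupuncture arm only is about p(1 − p): 0.30 × 0.70 = 0.21 at m = 0.1 and 0.79 × 0.21 = 0.17 at m = 0.2, as in the table. With recovery of 0.8 SD and a true acupuncture effect of 0.2 or 0.35 SD, both arms are significant in 100% of runs, so the pattern never appears. The between-arm rank-sum test on change detects those effects in 44% and 88% of runs.

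**The case against.** The strongest reply is that the article never says signed-rank or paired. Wilcoxon is also the name of the rank-sum test, and the qualifier may only describe the data: four visits, with arms compared at each visit or on change. The stated aim of comparing two strategies, and the two-row tables in the same section, point to a between-arm intent. On that reading the error rate is about 5% per test (4.2% to 5.6% above). This stands as to intent, and a reader should not infer that the trial will certainly run a paired test. It does not rescue the sentence: the qualifier would then be wrong, and the score and visit to be compared would remain open.

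A reader might also infer that natural recovery makes the test significant whatever acupuncture does. The article does not support that without a condition. It gives no recovery size, and at 0.1 SD the figure is only about 30%. Nor does any section say that within-arm P values will be the evidence of efficacy.

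A third tempting inference is that a primary outcome will fall under this rule. That is plausible for the Barthel Index but not shown. No distribution is given, the Barthel Index is also grouped into three classes that might be handled as categorical data, and nothing suggests that the 49-item SS-QOL total would fail a normality check.

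Finally, a journal article condenses a fuller plan, and model factors or the exact contrast may be set there. That excuses missing detail. It does not excuse a named method that does not fit the design.

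**Conclusion.** The point holds in a limited form. The article states a rule for non-normal quantitative outcomes whose most literal meaning is a within-patient test, and that test does not address the comparison the trial was set up to make. The alternative meaning would compare arms, but it contradicts the sentence's own qualifier. Either way, no valid between-arm analysis is fixed for scores that come under the rule.

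The figures of about 30%, 79% and 94-100% are conditional on the paired reading, 1:1 allocation, no acupuncture effect and the assumed recovery of 0.1, 0.2 and 0.3-0.5 SD. They show that a within-arm result cannot distinguish acupuncture from recovery. They are not the false-positive rate of the trial, because the article does not say that such results will decide it.

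**What to change.** Delete the sentence on the Wilcoxon test and the rule that selects the test by observed normality. Name one between-arm analysis for the quantitative outcomes that applies whatever their distribution. For example: a repeated-measures mixed model with arm, visit, arm-by-visit interaction and baseline score, reporting the difference between arms at the stated visits. As the non-parametric check, name a between-arm rank-sum test, or a rank analysis of covariance, on change from baseline at each stated visit. State that any within-arm before-after test is descriptive and is not evidence of an acupuncture effect.

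The cost is a wording change and a little more programming. No change to design, sample size or data collection is needed.

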## Discussion

Acupuncture is widely used to enhance stroke recovery in Eastern countries. However, a recent randomized controlled trial demonstrated that acupuncture has no specific efficacy in stroke rehabilitation [17]. A meta-analysis of sham-controlled randomized clinical trials concluded that there is insufficient evidence to support the use of acupuncture for functional recovery after stroke [18]. These data have led to ongoing controversy regarding the use of acupuncture therapy after stroke, despite the thousands years of evidence from traditional Chinese medicine practice.

The occupational therapists’ technique in the manipulation and selection of acupoints is the most important factor that determines the efficacy of acupuncture therapy [19]. In the present study, all occupational therapists are experts with more than ten years of acupuncture practice and plenty of experience with stroke treatments. The acupoints selected in this trial correspond to a complex prescription for stroke therapy originating in over 60 years of clinical application. Moreover, all the occupational therapists will receive special training to achieve a sound understanding of the acupoint selection and to normalize the practices across different therapists. The trial complies with the STRICTA (STandards for Reporting Interventions in Controlled Trials of Acupuncture).

The efficacy of acupuncture is different at different levels of stroke severity. It may have limit efficacy in very severe strokes, particularly in cases of extensive brain damage [20,21]. However, for mild or moderately severe strokes, acupuncture might be a superior treatment. In this trial, we will recruit patients with moderately severe acute strokes without severe deformity, and with NIHSS grades from 4 to 21, Glasgow Coma Scores of greater than or equal to 7, and mRS grades of less than or equal to 1.

Recovery of function after stroke is a long steady process that continues for several weeks or even months before reaching a stable phase. The effects of acupuncture occur within the same time frame. Several previous studies did not show any beneficial effect of acupuncture, and this may in part be explained by an assessment of efficacy too soon after acupuncture treatment (in most cases 2–3 weeks after stroke) [22,23]. An assessment or reassessment at a minimum of 4 weeks, and ideally at least 3 to 6 months after the completion of treatment is essential. We followed the time course of the normal process of stroke recovery in designing our study protocol. Thus, we will assess efficacy at baseline and at 4, 12 and 24 weeks after acupuncture intervention.

The primary endpoint for this study is the change in the quality of life in the intervention and control groups, from baseline to 4, 12 and 24 weeks post-therapy. Neurological deficits, disability, and dependence in activities of daily living will be evaluated by NIHSS and mRS as the secondary endpoints.

Many acupuncturists consider the main effect of acupuncture on the human body after stroke to be the rehabilitation of motor function, whereas few have considered the patients’ life quality, which includes factors such as dependence in activities of daily living, feeding, dressing, and continence of bowels and bladder. To address this, we will use the BI and SS-QOL questionnaires to measure the quality of life as the primary outcomes.
